## Abstract

**Background:**

Dietitian-led medical nutrition therapy (MNT) is an effective and cost-efficient strategy for improving dietary adherence and glycemic control in adults with type 2 diabetes (T2D). However, culturally adapted MNT interventions that account for local food systems, food security, and sociocultural eating practices remain scarce in African contexts. This paper describes the development of *Objectif Santé Diabète Bénin* (OSanDiaBé), a culturally tailored, dietitian-led MNT intervention designed to improve dietary adherence and glycemic control among adults with T2D in Benin, West Africa, using the Obesity-Related Behavioral Intervention Trials (ORBIT) model.

**Methods:**

To design OSanDiaBé, we use a hybrid framework integrating the ORBIT model with ecological validity and cultural adaptation approaches. In Phase Ia (Define), we developed a theory-driven model to identify key behavioral targets and hypothesized pathways linking a culturally tailored MNT intervention to dietary adherence and glycemic control. Phase Ib (Refine) involved adapting and refining an MNT intervention that combines evidence-based menu plans grounded in the 4A food security framework with individual nutrition counseling and group diabetes education. Intervention refinement was informed by mixed-methods data collected from 512 adults with T2D, including quantitative assessments, focus group discussions, sensory evaluations, and a stakeholder workshop, to enhance feasibility, acceptability, and cultural relevance.

**Expected outcomes:**

Phase II will evaluate feasibility, acceptability, and preliminary signals of effectiveness, including dietary adherence and glycemic control (HbA1c), prior to planned Phase III efficacy and Phase IV effectiveness trials.

**Conclusions:**

OSanDiaBé offers a replicable framework for culturally tailoring MNT interventions in low-resource settings. By integrating food security, culturally relevant dietary guidance, and family-centered nutrition support, this approach has the potential to strengthen diabetes nutrition care and reduce inequities in access to effective MNT across African contexts.

## Introduction

1

Over the past decade, the prevalence of type 2 diabetes (T2D) in Africa has surged by 129%, with an estimated 55 million adults currently affected (1, 2). Beyond its clinical consequences, T2D imposes substantial burdens on families, communities, and health systems, contributing to increased healthcare costs, reduced productivity, and adverse mental health outcomes (3–5). Addressing this burden requires effective diabetes management strategies that extend beyond pharmacological treatment and are responsive to local sociocultural, economic, and food system contexts.

Strong evidence demonstrates that adherence to nutrition therapy guidelines improves glycemic control, reduces cardiovascular risk factors, and lowers diabetes-related complications in adults with T2D (6, 7). However, sustained dietary adherence remains challenging, as management often requires long-term changes to established eating patterns, including increased consumption of whole grains, lean proteins, and healthy fats, alongside reduced intake of refined carbohydrates and sodium (8–12). These changes are particularly difficult to maintain in settings characterized by limited nutrition knowledge, constrained household resources, and competing social and occupational demands (13). Additional barriers include limited family support, cultural incongruence of prescribed diets, economic constraints on food access, and inconsistent or conflicting dietary advice from healthcare providers (9, 14–17). Together, these challenges highlight the need for simplified, culturally relevant dietary guidance that aligns with local food systems and household decision-making contexts.

Dietitian-led medical nutrition therapy (MNT) is increasingly recognized as an effective and cost-efficient strategy for improving dietary adherence, lowering hemoglobin A1c (HbA1c), and supporting weight management in adults with T2D (18, 19). As the dietetics profession expands in Africa (20), dietitian-led MNT offers an opportunity to deliver standardized, evidence-based nutrition care through individualized counseling and structured education. However, much of the existing evidence base originates from high-income Western contexts, and few interventions in African settings have been systematically developed using staged, theory-driven translational models. Moreover, diabetes self-management education programs in low-resource settings often face challenges related to feasibility, acceptability, and sustainability, reflecting socioeconomic constraints and limited cultural adaptation (21, 22). These gaps underscore the need for interventions that are both contextually grounded and scalable within routine health systems (23, 24).

The present project aims to develop a culturally tailored, dietitian-led MNT intervention for adults with T2D that targets dietary adherence as the primary behavioral outcome and glycemic control as the primary biomedical outcome. The intervention integrates menu plans based on the 4A framework of food security—adequacy, affordability, accessibility, and cultural acceptability (25)—with individual nutrition counseling and group diabetes education. Intervention development is guided by the Obesity-Related Behavioral Intervention Trials (ORBIT) model, a systematic framework for the staged development and testing of behavioral interventions prior to large-scale efficacy trials (26). The ORBIT model comprises sequential phases, including defining behavioral targets and hypothesized mechanisms (Phase Ia), refining intervention components through formative and pilot work (Phase Ib), evaluating feasibility and preliminary efficacy (Phase II), and assessing efficacy and effectiveness in subsequent trials (Phases III and IV). Its emphasis on theory-driven development, contextual adaptation, and progression criteria aligns closely with the implementation-oriented focus of nutrition and public health research in low-resource settings (9, 14–17, 26–31).

This paper describes the development of *Objectif Santé Diabète Bénin* (OSanDiaBé), a culturally tailored, dietitian-led MNT intervention designed to improve dietary adherence and glycemic control among adults with T2D in Benin, West Africa. We present the theoretical framework, the cultural adaptation and refinement process, and the planned feasibility and pilot testing phases. Consistent with ORBIT Phase Ia objectives, this study addresses the following research question: What behavioral targets, contextual factors, and intervention components are required to develop a culturally tailored, dietitian-led MNT program capable of improving dietary adherence and glycemic control among adults with T2D in Benin ?

## Methods

2

The development of OSanDiaBé was guided by the ORBIT model, a systematic and iterative framework designed to support behavioral intervention development prior to large-scale efficacy testing (26, 27). As illustrated in Figure 1 and described below, the ORBIT model emphasizes progressive refinement of intervention components to establish feasibility, acceptability, and cultural relevance before formal evaluation of efficacy and effectiveness. This framework is well suited to complex chronic disease management, such as T2D, where sustainable behavior change depends on addressing contextual, cultural, and psychosocial factors. Accordingly, analytical strategies across ORBIT phases were selected to align with the primary objective of intervention development. Descriptive and exploratory analyses were used to inform early-stage refinement, with increasing analytical complexity reserved for subsequent feasibility, pilot, efficacy, and effectiveness trials.

**Figure 1 F1:**
[figure not shown]
Summary of the ORBIT model [26, 27] applied to the development of ‘Objectif Santé Diabète Bénin' (OSanDiaBé) program for T2D in Africa, enabling progress and refinement based on new findings.

### Phase Ia: define

2.1

In Phase Ia (Define), we developed a theory-driven model to articulate the behavioral problem, identify key intervention targets, and specify hypothesized pathways through which behavior change may influence clinical outcomes, consistent with the ORBIT framework. As illustrated in Figure 2, this model integrates the ORBIT Phase Ia process with a conceptual representation of how a culturally tailored, dietitian-led MNT intervention may improve dietary adherence and glycemic control among adults with T2D.

**Figure 2 F2:**
[figure not shown]
Application of the ORBIT model and theoretical framework guiding Phase Ia (Define) of the OSanDiaBé intervention.

The model identifies dietary adherence as the primary behavioral target and addresses personal, familial, and environmental barriers commonly reported by adults with T2D in Benin. These barriers include limited nutrition knowledge, difficulties translating dietary recommendations into daily practice, cultural acceptability of prescribed diets, family dynamics, and economic constraints affecting food access. Identification of these barriers, informed by prior literature and formative engagement with local stakeholders, guided both the selection of intervention components and the specification of hypothesized mediating mechanisms.

We hypothesized that participation in the culturally tailored OSanDiaBé intervention—delivered through menu plans grounded in the 4A food security framework, individual nutrition counseling, and group diabetes education—would lead to improved dietary adherence and reductions in HbA1c. These effects were expected to be mediated by improvements in nutrition knowledge, family functioning, and self-efficacy, constructs supported by behavioral and social-cognitive theory. Improved dietary adherence was further hypothesized to result in better glycemic control and, over time, a reduced risk of diabetes-related complications, including organ damage and cognitive impairment. This theoretical model guided the development of intervention components and informed the selection of mediators examined in Phase Ib analyses.

### Phase Ib: refine

2.2

In Phase Ib (Refine), we developed and refined the OSanDiaBé intervention components using an iterative, mixed-methods approach to enhance feasibility, acceptability, cultural relevance, and implementation fidelity, consistent with the ORBIT framework (Figure 1). This phase focused on refining both intervention content and delivery strategies through the systematic integration of quantitative and qualitative evidence. Quantitative data were used to characterize dietary adherence, family functioning, and glycemic control and to explore theory-informed relationships relevant to intervention refinement. Qualitative methods, including focus group discussions (FGDs), sensory evaluation, and stakeholder workshops, provided in-depth insights into cultural norms, perceived barriers and facilitators to dietary adherence, and the acceptability of proposed intervention components. Findings from these complementary data sources were triangulated to inform iterative modification of the intervention prior to feasibility and pilot testing.

#### First stage of intervention manual development

2.2.1

The OSanDiaBé intervention manual was developed to operationalize the theoretical model defined in Phase Ia by translating identified behavioral targets and hypothesized mechanisms into culturally appropriate intervention components. A problem-formulation approach was employed to ensure that the intervention addressed the dietary, familial, and contextual barriers to adherence commonly reported by adults with T2D in Benin (32).

Intervention content and structure were informed by a theory of change, a comprehensive literature review, and formative qualitative research conducted with 32 adults with T2D, alongside consultations with 16 academic partners and 12 community partners in Benin (15–17). This formative work guided decisions regarding session content, delivery format, language and literacy level, recruitment materials, and participant engagement strategies.

Building on this foundation, evidence-based components were selected from established MNT and group education programs, including the Meta Salud Diabetes (MST) program (33) and the Pure Prairie Living Program (PPLP) (34, 35), both of which have demonstrated effectiveness in improving dietary understanding and addressing personal and environmental barriers to adherence. These components were systematically adapted using culturally adapted evidence-based practice approaches (36) and the ecological validity model (EVM) (37) to ensure alignment with local food systems, family structures, language, and health beliefs, as summarized in Table 1.

**Table 1 T1:** Ecological validity model.

**Domain**	**Dimensions**	**Adaptations in the intervention**
**Language**	Culturally appropriate and culturally syntonic	Translation of materials into French (official language in Benin)
**Persons**	Attributes of persons involved and their relationship	Involvement of patients' partners to enhance support for healthy eating and lifestyles in households.
**Metaphors**	Culturally consonant sayings and stories.	Use of role plays, games, and storytelling to present the skills being taught in more relatable ways.
**Contents & concepts**	Concepts consonant with culture and context	Integration of culturally relevant MNT concepts and important lifestyle intervention topics.
**Goals**	Supportive of adaptive values of culture	Integration of patient behaviors with family communication skills alongside the MNT goals.
**Methods**	Strategies consonant with patients' culture	Use of visual aids and simple definitions to describe the content clearly.
**Context**	Consideration of contextual factors	Integration of menu plan based on the 4A framework and what-up messages for reminding, encouraging, motivating, and self-efficacy.

The intervention integrates individual nutrition counseling with group education to target multiple mechanisms of behavior change. Group sessions were designed to enhance family involvement, strengthen coping skills, and increase self-efficacy through guided practice, goal setting, and progress monitoring, while individual sessions supported personalized dietary planning and goal refinement. Consistent with MNT practice guidelines and prior behavioral interventions (38, 39), the program was structured to include 12 sessions, (four individual and eight group), considered sufficient to support knowledge acquisition, skill development, and the adoption of sustainable dietary behaviors (40–42).

#### Intervention manual refinement

2.2.2

Refinement of the OSanDiaBé intervention manual employed a mixed-methods approach combining quantitative surveys, FGDs, sensory evaluation, and stakeholder workshops. This approach was designed to assess feasibility, acceptability, and cultural relevance of intervention components; validate proposed menu plans; and inform the integration of key actors, particularly family members and dietitians, into intervention delivery.

**In the quantitative stage**, participants were recruited from outpatient diabetes units of six secondary health centers in Benin (two public and four private). Eligible participants were adults aged 40–65 years with a documented diagnosis of T2D for at least 1 year, self-identified as Beninese, and willing to provide informed consent. Individuals with severe health conditions that could limit their ability to complete questionnaires or participate in anthropometric or biological assessments were excluded. The selected age range reflects the population most affected by T2D and its complications in Benin and sub-Saharan Africa and reduced heterogeneity in dietary behaviors and disease management experiences during intervention development. Requiring a minimum diabetes duration of 1 year ensured participants had prior exposure to diabetes self-management education and dietary recommendations, allowing meaningful assessment of dietary adherence, family functioning, and culturally embedded practices relevant to intervention refinement.

A total of 512 eligible participants were enrolled, consistent with recommendations for exploratory and formative research (43). Data collection included validated measures of dietary adherence, family functioning and support, cultural identity, and sociodemographic characteristics (age, sex, marital status, education, employment, income, ethnicity, and diabetes duration). Anthropometric measurements (height, weight, waist and hip circumference) and laboratory assessment of glycemic control (HbA1c) were also conducted.

**In the qualitative stage**, to complement quantitative findings, a random subsample of 94 participants was invited to participate in eight FGDs, consistent with qualitative research recommendations (44). Using a semi-structured guide, discussions explored understanding of food-based dietary guidelines, perceived barriers and facilitators to dietary adherence, acceptability and feasibility of proposed MNT components, perceptions of body size and obesity-related risks, and family dynamics related to food and diabetes management.

In addition, 30 participants (15 adults with T2D and 15 without T2D) were recruited to evaluate the acceptability of proposed dietary menus using sensory testing methods. Fourteen daily menus were developed using a linear goal programming model to optimize nutritional adequacy, affordability, accessibility, and cultural acceptability; detailed methods have been published previously (45). During sensory evaluation, trained participants rated packaged food samples using a five-point hedonic scale to assess overall acceptability (46).

Finally, a stakeholder workshop was conducted with 14 professionals involved in diabetes prevention and care, including dietitians, nutritionists, pharmacists, physical activity specialists, and endocrinologists, identified in collaboration with the Directorate of Health Services. The workshop focused on intervention delivery, recruitment strategies, cultural considerations, and implementation feasibility. All FGDs and workshops were digitally audio-recorded and transcribed for analysis.

#### Quantitative analysis: phase Ib

2.2.3

All quantitative analyses were conducted using Stata (version 19; StataCorp LLC, College Station, TX, USA). Consistent with the objectives of ORBIT Phase Ib, analyses were designed to inform intervention refinement rather than to test intervention effectiveness.

Descriptive statistics, including means and standard deviations for continuous variables and frequencies and percentages for categorical variables, were used to summarize participant sociodemographic characteristics, dietary adherence, family functioning, and glycemic control. These analyses provided foundational information to guide refinement of intervention content, delivery strategies, and participant engagement approaches.

To examine hypothesized pathways specified in the Phase Ia theoretical model (Figure 2), mediation and moderation analyses were conducted using structural equation modeling (SEM) (47). These analyses assessed relationships among family functioning, dietary adherence, and glycemic control to identify psychosocial mechanisms relevant to intervention development and prioritization of intervention components. All SEM models were adjusted for age, sex, education level, diabetes duration, body mass index, health center, marital status, work status, and social support, variables known to influence dietary adherence and glycemic control, to reduce potential confounding (48, 49).

### Phase IIa: proof-of-concept

2.3

Phase IIa will be conducted following completion of Phase Ib, as findings from the refinement phase are essential to determine the readiness of the OSanDiaBé intervention for feasibility testing. Consistent with the ORBIT framework, the primary objective of Phase IIa is to assess the feasibility and acceptability of the culturally tailored, dietitian-led MNT intervention using a mixed-methods design. We hypothesize that key feasibility indicators, including recruitment, retention, and session attendance, along with participant satisfaction and acceptability, will exceed 75%, indicating readiness for pilot testing in Phase IIb.

#### Phase IIa sample

2.3.1

A single-arm feasibility design will be used to enroll 30 adults with T2D. Eligible participants will (1) self-identify as Beninese; (2) be aged 40–65 years; (3) have a clinical diagnosis of T2D for at least one year; (4) have an HbA1c level >7% at enrollment; (5) have a family member willing to participate or provide ongoing support; and (6) be willing to commit to the study protocol and attend scheduled sessions. Participants will be recruited from the pool of 512 individuals who participated in Phase Ib. The sample size of 30 was selected in accordance with recommendations for pre-pilot and feasibility studies (43). The intervention will include two individual sessions (45–60 min each) and eight group sessions (90–120 min each). Sessions will be delivered by six trained dietitians or nutritionists, with each group of 10 participants assigned two facilitators experienced in health promotion, trained in MNT, and committed to maintaining protocol fidelity.

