**Figure 3 F3:**
[figure not shown]
Schematic diagram of the feasibility study for the new cultural tailored medical nutrition therapy.

To support future replication and scalability, feasibility and acceptability outcomes will be evaluated using the RE-AIM (Reach, Effectiveness, Adoption, Implementation, and Maintenance) framework (52). Feasibility indicators will include recruitment strategies, session attendance, retention rates, and facilitator fidelity assessed through session observations. Acceptability will be measured using participant-reported perceptions of cultural relevance, perceived benefits, and overall satisfaction. Although Phase IIa is not designed to test efficacy, exploratory assessments of behavioral and biomedical outcomes will be conducted at baseline and 12 weeks post-intervention. Dietary adherence will be assessed using a multi-method approach combining the Perceived Dietary Adherence Questionnaire (PDAQ) adapted to the Benin Food Guide (53), dietary intake from the modified UKDDQ, and facilitator-rated behavioral monitoring (e.g., meal planning, food preparation, and physical activity practices) (51). Family functioning will be measured using the McMaster Family Assessment Device (54), diabetes knowledge using the ADKnowl questionnaire (55), and self-efficacy using the Diabetes Self-Efficacy Scale (DSES) (56). Anthropometric and clinical measures, including weight, height, waist circumference, blood pressure, and HbA1c—will also be collected with informed consent. Qualitative feedback from participants and facilitators will be analyzed to identify themes related to communication, comprehension, engagement, and perceived cultural relevance. Transportation incentives will be provided to facilitate participation in sessions and follow-up assessments.

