#### Phase IIb sample

2.4.1

A total of 60 adults with T2D will be enrolled and randomized in a 1:1 ratio to either the intervention group (OSanDiaBé) or a wait-list control group receiving usual care. Randomization will be conducted after screening and informed consent using a computer-generated randomization sequence. To minimize potential bias, the principal investigator will be aware of group allocation, while physicians, data collectors, and laboratory personnel will remain blinded. Participants will be informed of their group assignment following randomization. The target sample size (*n* = 60; 30 per group) is consistent with recommendations for pilot randomized trials and is intended to support intervention refinement and effect size estimation for subsequent efficacy studies (58). Findings from Phase IIa will further inform final sample size considerations for later trials.

Participants will be recruited from six collaborating health centers using provider referrals, peer referrals, flyers, and word-of-mouth outreach. Eligibility criteria include: self-identification as Beninese; age 40–65 years; a clinical diagnosis of T2D for ≥1 year; uncontrolled diabetes (HbA1c >7%); availability of a supportive family member; and ability to provide written informed consent. Participants must be deemed suitable for group-based education and general dietary and lifestyle guidance by the referring healthcare provider. Exclusion criteria include pregnancy, recent major cardiovascular events (e.g., stroke or congestive heart failure), clinical conditions requiring specialized dietary management, or current participation in a similar nutrition program, to minimize contamination and ensure participant safety.

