### Possible pitfalls and alternative strategies

3.3

A key challenge is the recruitment and retention of participants with limited prior exposure to MNT research. While strong community partnerships and formative engagement support current recruitment strategies, alternative approaches—such as collaboration with religious institutions, community leaders, and local organizations—will be implemented if recruitment targets are not met. To promote retention, participants will receive transportation compensation, flexible scheduling, and culturally responsive counseling tailored to individual and family needs. For participants unable to attend sessions in person, home-based counseling will be offered to maintain engagement and intervention fidelity. If Phase IIa identifies low feasibility or acceptability, targeted mixed-methods analyses will be conducted to identify underlying barriers, and intervention components will be adapted accordingly before progression to subsequent phases. This iterative process, consistent with the ORBIT framework, ensures that the intervention is optimized for effectiveness, scalability, and sustainability in real-world settings.

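### Phase IIa recruits only from Phase Ib participants, so its recruitment rate above 75% cannot indicate readiness for Phase IIb, which recruits by referral, flyers and word of mouth

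*Protocol article*

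**What the plan says.** Three statements in the protocol article bear on this point.

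- **The readiness criterion** (2.3, Phase IIa: proof-of-concept). For the named indicators (acceptability, satisfaction, attendance, retention and recruitment) the hypothesis is that each "will exceed 75%, indicating readiness for pilot testing in Phase IIb". Recruitment is the first indicator that the article names. Section 2.3.2 (Phase IIa procedures) repeats the theme: "Feasibility indicators will include recruitment strategies, session attendance, retention rates, and facilitator fidelity assessed through session observations".
- **The Phase IIa source** (2.3.1, Phase IIa sample). "A single-arm feasibility design will be used to enroll 30 adults with T2D", and "Participants will be recruited from the pool of 512 individuals who participated in Phase Ib". No other source is named.
- **The Phase IIb source** (2.4.1, Phase IIb sample). "Participants will be recruited from six collaborating health centers using provider referrals, peer referrals, flyers, and word-of-mouth outreach". The target is 60, randomised 1:1.

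Section 3.3 (Possible pitfalls and alternative strategies) adds the sponsor's own view of the risk: "A key challenge is the recruitment and retention of participants with limited prior exposure to MNT research". The limitations in 3.2 cover region, age range and diabetes duration, but not the source of the Phase IIa sample.

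**The concern.** A feasibility rate informs the next phase only if it is measured under conditions that resemble that phase. For recruitment, the relevant condition is how patients are found and asked. Phase IIa asks people who have already consented to this project, completed its questionnaires and had HbA1c measured. Phase IIb depends on referrals and outreach to bring patients forward. These are different processes, and the first says little about the yield of the second.

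At stake is what may be concluded at the end of Phase IIa. A high recruitment figure could be reported as readiness for the pilot although the pilot's recruitment route has not been tried. Section 3.3 promises adaptation if Phase IIa shows low feasibility. A recruitment problem specific to the Phase IIb channels would not appear in Phase IIa, so it would not trigger that step.

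**Working it through.** **1. The plan's own figures.** The sample of 30 rests on a cited recommendation, with no precision or power target, so there is no calculation to reproduce. The staffing is consistent: 30/10 = 3 groups, and 3 × 2 facilitators = 6, as stated.

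**2. The two recruitment processes side by side.**

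| | Phase IIa (2.3.1) | Phase IIb (2.4.1) |
|---|---|---|
| Source | 512 Phase Ib participants | Open recruitment at six centers |
| Route | Contact method not stated | Provider and peer referral, flyers, word of mouth |
| Earlier consent to this project | All | Not required, not excluded |
| Number | 30 | 60 |

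The core eligibility criteria agree: Beninese, age 40–65, type 2 diabetes for at least one year, HbA1c above 7%, a supportive family member. The difference lies in source and route, which are what a recruitment rate measures.

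**3. What passing on recruitment would mean.** Assume the rate is enrolled divided by approached; the article does not define the denominator. With 30 enrolled, a rate above 75% needs fewer than 30/0.75 = 40 approaches, so at most 39 (30/39 = 76.9%). That is 39/512 = 7.6% of a pool of earlier participants. The result contains no information on referral or outreach.

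**4. Illustration for Phase IIb.** Eligible approaches needed to fill 60 places = 60 / acceptance rate. All rates are assumed.

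| Acceptance | Calculation | Approaches |
|---|---|---|
| 85% | 60/0.85 = 70.6 | 71 |
| 75% | 60/0.75 = 80 | 80 |
| 65% | 60/0.65 = 92.3 | 93 |
| 50% | 60/0.50 = 120 | 120 |

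If prior participants accept at 85% and new patients at 50%, the shortfall is 120 − 71 = 49 approaches, and Phase IIa could not show it.

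**5. Indicators counted per enrolled person (such as retention).** The smallest count above 75% is 23 of 30 (76.7%), with an exact 95% interval of 57.7% to 90.1%. The probability of passing is P(X ≥ 23), with X binomial (30, p):

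| Assumed true rate p | P(pass) |
|---|---|
| 0.65 | 0.12 |
| 0.70 | 0.28 |
| 0.75 | 0.51 |
| 0.80 | 0.76 |
| 0.85 | 0.93 |
| 0.90 | 0.99 |

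If the true rate were 10 to 20 points higher in prior participants than in openly recruited patients (say 85% against 65–75%), the criterion would usually be met in the first group (0.93) and met much less often in the second (0.12–0.51). Nothing in the article shows whether such a gap exists. The table shows only how sensitive the criterion would be to one.

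**The case against.** The case for leaving the plan alone has real strength.

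- A known pool is a defensible convenience sample for a single-arm proof of concept. HbA1c was measured in Phase Ib, so patients above 7% are easier to find.
- Phase Ib was a survey with measurements, and focus groups for a subsample. It delivered no nutrition therapy. Phase IIa is therefore the first real test of attendance, retention and acceptability.
- Phase IIb is itself a pilot before a powered trial, so open recruitment will be exercised before Phase III. Section 3.3 also offers other recruitment routes if targets are missed.
- Phase Ib enrolled 512 people at six centers. That was a less demanding study, but it bears on whether 60 can be found.

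All of this stands. It limits the point to recruitment but does not rescue the recruitment indicator, because the article still reads that indicator as readiness for Phase IIb.

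A reader might infer more than the article supports:

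- *That Phase IIb enrols only patients new to research.* Section 2.4.1 does not exclude former Phase Ib participants, and its centers may be the same six.
- *That the Phase IIa pool leaves out the patients whom 3.3 worries about.* Someone who answered a survey may still have had little contact with nutrition-therapy research.
- *That no Phase IIb channel is used in Phase IIa.* The article names a source, not a contact method.
- *That the sample helped to design the intervention.* A random subsample of 94 was invited to focus groups: 94/512 = 18.4%, or about 0.184 × 30 = 5.5 of 30 under proportional sampling.

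**Conclusion.** The point holds for the recruitment indicator and should be corrected. Source, threshold and Phase IIb route are all stated, and they do not fit together: a recruitment rate from a closed pool of prior participants does not estimate uptake through referral, flyers and word of mouth. This follows from the stated design and needs no assumed figure.

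For retention, attendance and acceptability the point is weaker. These are genuine first measurements, in people selected for earlier participation. Some optimism is plausible, but its size is unknown. It would be tempting to conclude that the whole readiness judgement fails or that these rates are known to be inflated; the article supports neither.

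The approach counts and pass probabilities rest on assumed rates and, for the figure of 39, on an assumed denominator. They illustrate the possible consequence and do not estimate it. The practical harm is a slower or harder start to Phase IIb and an unsupported statement about readiness. No Phase IIb result is made invalid.

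**What to change.** 1. In 2.3, remove recruitment from the indicators whose exceeding 75% signals readiness for Phase IIb, or report it only as uptake among prior participants.
2. In Phase IIb, record eligible patients approached and enrolled by source (provider referral, peer referral, flyer, word of mouth), and make recruitment by channel a criterion before Phase III.
3. State, in 3.2 or with the Phase IIa results, that the Phase IIa retention and acceptability rates come from people who had already taken part in Phase Ib.

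The cost is small: changed wording and a screening log by source, with no extra patients. The downside is that Phase IIb starts without a prior recruitment figure.

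Recruiting part of Phase IIa through the Phase IIb channels, and reporting by source, is an option for the sponsor rather than a required change. It would give an early look at the channels, but new patients would need HbA1c screening. With an even split each source would have 15 people, so one person moves a rate by 1/15 = 6.7 points.
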